## Abstract

**Background:**

Impairments in balance control and falls are common problems for people with multiple sclerosis (PwMS), resulting in mobility limitations and reduced participation. Non-invasive neuromodulation techniques such as functional electrical stimulation (FES) and transcutaneous spinal stimulation (TSS) have revealed promising results in improving motor functions in other neurological populations; however, their effects during task-specific balance training have not been investigated in PwMS.

**Objective:**

To evaluate the feasibility, acceptability, safety, and preliminary clinical efficacy of neuromodulation-augmented balance training programs on balance, mobility, and neuroplasticity in PwMS (ClinicalTrials.gov Identifier: NCT07174973).

**Methods:**

Twenty-four ambulatory PwMS will be randomly assigned into three groups: (1) visual feedback balance training (VFBT) with sham stimulation, (2) VFBT with active (closed-loop) FES for the ankle muscles and sham TSS, and (3) VFBT with active FES and active (open-loop sub-motor-threshold) TSS at the lumbosacral enlargement. Participants in each group will complete 12 training sessions over six weeks. Feasibility, safety, and acceptability will be assessed through recruitment and adherence metrics, adverse-event monitoring, and semi-structured interviews guided by the Technology Acceptance Model questionnaire-2. Performance-based measures of balance, mobility, and walking speed, as well as patient-reported outcomes of balance confidence, walking ability, and fear of falling will be recorded to assess the preliminary efficacy. Modulation in neural pathways excitability will be quantified by recording motor evoked potentials and spinal motor evoked potentials.

**Conclusion:**

Findings will help to determine whether neuromodulation-augmented balance training is feasible, safe, and acceptable for PwMS and will guide the design of a future fully powered RCT.

## 1. Introduction

More than 75% of people with multiple sclerosis (PwMS) exhibit some degree of postural imbalance, even in the early stages of the disease [1–6]. Deficits in balance control are considered significant risk factors for falls, resulting in diminished physical activity and participation [1–6]. Although evidence supports the effectiveness of exercise-based training programs in PwMS to improve balance [2,3,7,8], these improvements are not sufficient to meaningfully mitigate fall risk [7]. Furthermore, the evidence is more limited in PwMS in comparison to other neurological populations, such as those with stroke and Parkinson’s disease, where more systematic reviews and clinical guidelines have been developed to improve mobility and prevent falls [9–15]. This highlights the need to develop innovative, task-specific, challenging rehabilitation programs to improve mobility and reduce falls in PwMS

The advent of rehabilitation technologies has facilitated the incorporation of interactive, game-oriented components into virtual and augmented training settings [16–22]. These methods have provided motivating and task-specific environments for people with neurological conditions, including spinal cord injury (SCI), stroke, and MS to practice motor skills [16–22]. The growing body of evidence also indicates that integrating non-invasive neuromodulation techniques such as functional electrical stimulation (FES) and transcutaneous spinal stimulation (TSS) into neurorehabilitation protocols can further improve motor function and promote neuroplasticity in people with neurological conditions [23–30]. FES can activate paralyzed or weak muscles and facilitate movements by selectively stimulating superficial motor nerves and/or muscles, however, it recruits motor units in a non-physiological pattern, which can result in rapid muscle fatigue [31–33]. TSS can activate multiple muscles by stimulating dorsal roots and modulating excitability across multiple spinal segments, potentially resulting in less muscle fatigue [34,35]. However, its ability to produce direction-specific movements required for balance corrections is limited compared to FES [28–30,36].

Our team has developed a balance training platform that integrates visual feedback balance training (VFBT) with closed-loop FES for ankle muscles [24,37,38]. We have tested the feasibility and preliminary efficacy of this protocol in individuals with incomplete SCI who had difficulty in balance but were still able to stand without support [24,39]. However, for individuals with lower levels of function, particularly those with knee and hip impairments, FES for the ankle muscles may be insufficient to provide the postural support necessary for effective balance training [27,40,41]. Although proximal muscles could be stimulated by additional FES channels, this would significantly increase the system’s complexity. Rather, TSS offers a more effective way to concurrently modulate excitability across several spinal segments [28–30,36], and to augment multi-muscle activation without adding technical burden. This synergistic interaction is supported by preliminary results from our research group in people with incomplete SCI, showing greater functional benefits when TSS is administered concurrently with closed-loop FES (TSS + FES) during balance tasks [42,43].

Given the novelty of this combined neuromodulation approach and the lack of feasibility data in PwMS, a pilot randomized controlled trial (RCT) is warranted before designing a fully powered RCT. Therefore, the main purpose of this study is to assess the feasibility, acceptability, safety, and adherence of neuromodulation-augmented balance training interventions in PwMS. The second purpose is to investigate the preliminary clinical efficacy on balance performance, mobility, balance confidence, fear of falling and neural excitability. We hypothesize that the intervention will be feasible and acceptable with minimal adverse events, and that the combined neuromodulation group (TSS + FES) will show greater functional and neurophysiological improvements than FES-only or sham stimulation groups.

## 2. Methods & materials

### 2.1. Participants & eligibility criteria

This multi-method study includes a pilot RCT to evaluate feasibility, acceptability, safety and preliminary efficacy of this novel neuromodulation-augmented balance training program and a qualitative descriptive study to capture patients’ experiences and perspectives [44]. This study will take place at the Lyndhurst Centre, a tertiary rehabilitation hospital, and has been approved by the University Health Network Research Ethics Board (Approval #25–5549, Version 5, December 29, 2025) and is registered at ClinicalTrials.gov (Identifier: NCT07174973). A formal sample size calculation is not required, as this is a pilot RCT [45]. We plan to recruit 24 participants (eight in each group), based on our previous studies in people with SCI using non-invasive neuromodulation.

For recruitment, we will use multiple strategies, including clinicians’ referrals, posting flyers at outpatient MS clinics, community MS programs, and existing research registries/databases (MS Canada). Participants will be allowed to continue their usual medical care throughout the study period. Written informed consent will be obtained from all eligible participants prior to baseline assessment. Given the small sample size, single-site design, and low-risk nature of the interventions, a formal independent data monitoring committee will not be required for this pilot RCT. Participant safety and study conduct will be monitored by the principal investigator, and any adverse events will be reported to the University Health Network Research Ethics Board. In addition, ongoing monitoring will occur through regular research team meetings to review recruitment progress, protocol adherence, intervention fidelity, data completeness, and adverse events.

Fig 1 shows the SPIRIT Timeline for the study, Table 1 summarizes the inclusion and exclusion criteria, and Table 2 shows the template for Intervention Description and Replication (TIDieR) checklist.

**Table 1 pone.0346491.t001:** Inclusion and exclusion criteria.

Criteria	
Inclusion	Confirmed diagnosis of MS based on the revised McDonald criteria Age 18–65 years Ability to walk at least 100 meters with or without an assistive device Self-reported balance difficulties during daily activities
Exclusion	Uncorrected visual impairments that interfere with balance testing Cognitive deficits limiting comprehension of study procedures MS relapse within the past 30 days Presence of other neurological or orthopedic conditions affecting balance Recent participation in structured rehabilitation within the past month Lower-limb botulinum toxin injections within the past three months Known peripheral nerve injuries Contraindications to electrical stimulation (e.g., implanted metal/electronic devices, pacemakers) Contraindications to TMS (e.g., seizure history, metallic implants in the head). Pregnancy

**Table 2 pone.0346491.t002:** The TIDieR checklist.

1. Brief Name	Visual Feedback Balance Training (VFBT) with (1) sham neuromodulation, (2) closed-loop functional electrical stimulation (FES), and (3) combined closed-loop FES and transcutaneous spinal stimulation (TSS + FES).
2. Why	To improve balance, mobility, and neuroplasticity in PwMS through task-specific balance training combined by neuromodulation. VFBT facilitates patient’s engagement and motor learning through real-time feedback; FES helps to activate ankle muscles and produces direction-specific ankle torques during balance training; TSS modulates spinal excitability to augment the effects of FES and supra-spinal control by voluntary contribution.
3. Who	Interventions will be delivered by trained clinical researchers with experience in balance rehabilitation and non-invasive neuromodulation using standardized procedures.
4. When	The intervention will be delivered to ambulatory PwMS who are clinically stable (absence of an MS relapse within the last 30 days)
5. What	**Materials** **VFBT:** Wii Balance Board (Nintendo, Japan), monitor display, ceiling-mounted safety harness. **FES:** stimulator: Myndsearch, MyndTec Inc., Mississauga, ON, Canada, surface electrodes (5 × 5 cm for dorsiflexors; 5 × 10 cm for plantarflexors). **TSS:** stimulator: Pajunk® GmbH Medizinprodukte, Geisingen, Germany, surface electrodes (5 × 10 cm) positioned over T10–L2 with anterior reference electrodes (5 × 5 cm) placed over the abdomen medial to the anterior superior iliac spine. **Procedures** Participants will perform static and dynamic standing balance tasks with real-time visual feedback regarding their postural sway. Tasks will include target tracking, ellipse tracing, color-matching, and hunting games. Neuromodulation (active or sham) is delivered concurrently according to group allocation.
6. Who	Interventions will be delivered by experienced clinical researchers who are trained in balance rehabilitation and using non-invasive neuromodulation.
7. How	In-person, one-on-one supervised sessions.
8. Where	University Health Network, Lyndhurst Rehabilitation Hospital.
9. How Much	12 sessions over 6 weeks (2 sessions/week). Each session will last approximately 90 minutes, consisting of setup, warm-up, 60 minutes of active training, and a cool-down.
10. How challenging	The balance training is designed to be progressively challenging and tailored to each participant’s abilities. VFBT difficulty will be increased by changing center-of-pressure excursion range, movement speed, and duration of the game. Warm-up balance exercises will be progressed from standing on a rigid, stable surface to standing on unstable surfaces, and eventually walking-based balance tasks.
11. Progression/Regression	Balance task difficulty will be progressed by increasing center of pressure excursion range, task speed, and the duration of each game.
12. Personalization	FES stimulation intensities will be individualized based on motor threshold and maximal tolerable intensity; balance task difficulty will be adjusted based on the participant’s baseline balance calibration by testing limits of stability; TSS will be delivered at a sub-motor threshold level
13. Protocol Deviation	No planned modifications. Any protocol deviations, such as changes in the stimulation intensity due to discomfort or fatigue will be documented.
14. How Well	Session attendance will be tracked; stimulation parameters will be recorded at each session. Adherence rates, and any protocol deviations will be reported
15. Harms	Adverse events will be monitored at each session (e.g., skin irritation, fatigue, dizziness, discomfort).

PwMS: people with multiple sclerosis, VFBT: visual feedback balance training, FES: functional electrical stimulation, TSS: transcutaneous spinal cord stimulation, TSS + FES: combined transcutaneous spinal cord stimulation and functional electrical stimulation, MEPs: motor evoked potentials, SMEPs: spinal motor evoked potentials, TAM: Technology Acceptance Model, COP: center of pressure, FU: follow-up.

**Fig 1 pone.0346491.g001:**
[figure not shown]
SPIRIT Timeline: Schedule of enrollment, interventions, and assessments. Legend: VFBT: Visual Feedback Balance Training, FES: Functional Electrical Stimulation, TSS: Transcutaneous Spinal Stimulation, TAM-2: Technology Acceptance Model-2, BBS: Berg Balance Scale; T25FW: Timed 25-Foot Walk, TUG: Timed Up and Go, ABC: Activities-specific Balance Confidence Scale, MSWS-12: 12-item Multiple Sclerosis Walking Scale, FES-I = Falls Efficacy Scale-International; GRC: Global Rating of Change, MEPs: Motor Evoked Potentials, SMEPs: Spinal Motor Evoked Potentials.

### 2.2. Randomization, allocation, and blinding

Participants will be randomly assigned into three groups following baseline assessment using a computer-generated covariate-adaptive algorithm, including two variables: (1) gender, and (2) baseline postural control using the forward reach test of the Berg Balance Scale (BBS). To ensure balanced allocation of people with different levels of function, participants with scores of 0–2 in the forward reach test (i.e., reaching forward ≤2 inches) will be categorized as having low postural control, while those with scores of 3–4 (i.e., reaching forward ≥5 inches) will be categorized as having high postural control. Outcome assessors conducting clinical assessment will be blinded to group assignment. The neurophysiological assessments will be conducted by one of the therapists delivering the intervention and will therefore not be blinded. Since the neurophysiological assessment involves standardized instrumentation, they are less susceptible to assessor bias [46]. Participants will remain blinded through the use of sham stimulation.

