**Fig 3 pone.0346491.g003:**
[figure not shown]
Measurement of corticospinal and spinal excitability. Motor evoked potentials (MEPs) are evoked by transcranial magnetic stimulation (TMS), and spinal motor evoked potentials (SMEPs) are evoked by transcutaneous spinal stimulation (TSS).

The coil will be placed over the primary motor cortex, and the hotspots will be searched manually by finding a spot that can elicit the largest response in the tibialis anterior with the lowest intensity. The location of the hotspot will be stored in the brain navigation system (Neuronavigation, Soterix Medical Inc.) to ensure a consistent stimulation location above the motor cortex at each time point [59]. Then, the resting motor threshold will be determined as the intensity of magnetic stimulation required to evoke MEPs with a peak-to-peak amplitude of 50 micro-V in at least 5 out of 10 consecutive trials. MEPs will subsequently be recorded at five stimulation intensities corresponding to 100%, 110%, 120%, 130%, and 140% of the session-specific RMT, with three trials collected at each intensity to characterize the stimulus–response relationship. To obtain a stable estimate of corticospinal excitability, an additional ten MEPs will be recorded at 120% RMT. To normalize MEP amplitudes, we will measure the maximal motor wave (M-max) in soleus and tibialis anterior after TMS testing. Soleus and tibialis anterior M-max will be measured by applying maximal single square pulses to the tibial nerve in the popliteal fossa and the common peroneal nerve around the head of the fibula, respectively.

Spinal motor evoked potentials (SMEPs) will be assessed with double-pulse stimulation (Digitimer, Model DS7A, Welwyn Garden City, UK) delivered over L1-L2 (two monophasic pulses with 1ms pulse width and a 50 ms inter-stimulus interval). Surface EMG will be recorded from the more affected side or dominant side in case of symmetrical involvement from four lower-limb muscles: soleus, tibialis anterior, rectus femoris, and biceps femoris. The same amplifier will be used to both amplify and band-pass-filter the data, as described above. Recruitment curves will be generated by increasing stimulation intensity from 5 mA to the participant’s maximal tolerable level in 5-mA increments. At each intensity, five paired-pulse stimulations were delivered with 5-second inter-trial intervals.

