## 3. Discussion

Non-invasive neuromodulation techniques, including FES and TSS, have shown efficacy in improving walking and upper limb motor functions when coupled with active task-specific training in people with neurological conditions [23,29,30,33,62–65]. However, their potential effects as complementary interventions to improve balance in PwMS have yet to be investigated. This pilot RCT aims to fill this gap by assessing the feasibility of integrating technology specifically non-invasive neuromodulation and task-specific balance training via VFBT and evaluating its effects on balance, mobility, and neuroplasticity in PwMS. Running this pilot study will help to identify methodological, logistical, and implementation-related challenges prior to conducting larger RCTs [66–69].

In addition to feasibility and acceptability outcomes, the study includes a battery of clinical and neurophysiological assessments. These exploratory measures will help to determine whether neuromodulation-augmented VFBT has the potential to improve balance, mobility, balance confidence, and fear of falling. Neurophysiological assessment will help to provide preliminary insight into whether changes in corticospinal and spinal excitability are associated with functional improvements. These mechanistic measures are recommended in neuromodulation trials to identify the underlying neural mechanisms associated with recovery and guide the design of future studies [28,60].

The methodological strengths of this study are consistent with high-quality trials. The randomized, sham-controlled, and assessor-blinded design reduces bias, and covariate-adaptive randomization helps to normalize baseline differences and reduce heterogeneity across groups [70–72]. Furthermore, incorporation of semi-structured interviews offers a more in-depth understanding of participants’ experiences and perspectives, which is of great importance when considering to integrate neuromodulation techniques into rehabilitation settings. Preliminary clinical outcomes will help to calculate the effect size and variance necessary to plan a definitive RCT.

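### After allocation the neurophysiological tests are run by an unblinded treating therapist, and the MEP at 120% of session-specific threshold cannot show a pure threshold gain unless the threshold itself is analysed

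*Protocol article*

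**What the plan says.** Section 2.2 separates two kinds of assessment. For the clinical tests, "Outcome assessors conducting clinical assessment will be blinded to group assignment". For the others, "The neurophysiological assessments will be conducted by one of the therapists delivering the intervention and will therefore not be blinded". The reason given is that "Since the neurophysiological assessment involves standardized instrumentation, they are less susceptible to assessor bias". The same section states the order of events: "Participants will be randomly assigned into three groups following baseline assessment".

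Section 2.4.6 describes the procedures. For the MEPs, "the hotspots will be searched manually by finding a spot that can elicit the largest response", and the site is then stored by neuronavigation so that the same location is used at each time point. RMT is the intensity that gives 50 micro-V in at least five of ten trials. MEPs are then taken at intensities "corresponding to 100%, 110%, 120%, 130%, and 140% of the session-specific RMT", three per level, with ten more at 120% RMT, and amplitudes are normalized to M-max. For the SMEPs, current rises from 5 mA to the "maximal tolerable level in 5-mA increments".

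The Introduction hypothesizes greater neurophysiological improvement with combined stimulation. Section 2.6 sends these outcomes to a group × time repeated-measures ANOVA. The Discussion says, without exception, "The randomized, sham-controlled, and assessor-blinded design reduces bias".

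**The concern.** Standardized equipment fixes amplification, filtering and pulse shape. It does not fix the intensity at which an operator accepts a threshold, or the point at which a participant asks to stop. Here the operator at both follow-up tests has also treated the participant and knows the arm.

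A second matter concerns the measurement scale and would remain under full blinding. If each visit's MEP intensities are tied to that visit's threshold, an intervention that lowers the threshold also lowers the stimulus used to look for its effect.

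At stake is the neurophysiological part of the hypothesis, and any effect size from these measures carried into planning the definitive trial. With eight participants per arm, a modest systematic influence would be hard to recognize in the data.

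**Working it through.** The plan gives no figure on this point to reproduce. The check sets the passages side by side and then illustrates the mechanism on assumed curves.

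**1. Who knows what, and when.** Randomization follows baseline assessment, so the baseline tests precede allocation. The post-training and 8-week tests come after it. Any influence from knowing the arm therefore enters the change from baseline, which is what the group × time term tests.

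**2. Which settings stay open after allocation.**
- *Hotspot.* The search is manual, but the site is stored for use at each time point. Read with the order of events, the search comes before allocation, so it is not a clear route for bias related to arm.
- *RMT.* The rule is numeric but noisy. With X ~ Binomial(10, p), P(X ≥ 5) is 0.367 at p = 0.4, 0.623 at p = 0.5 and 0.834 at p = 0.6. An intensity below threshold (p = 0.4) passes about 37% of the time. One exactly at threshold fails 1 − 0.623 = 0.377 of the time. This leaves room for small errors in either direction.
- *SMEP ladder.* The steps are absolute. The top depends on what the participant tolerates.

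**3. Threshold-only effect, MEP at 120% RMT.** Assumed curve: MEP(I) = A / (1 + exp((S50 − I)/k)), with I in % of stimulator output. RMT is where MEP = 0.05 mV, so RMT = S50 − k·ln(A/0.05 − 1). Assumptions: baseline RMT 50; k = 4, 6 or 8; A = 0.5, 1 or 2 mV.

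Worked case, k = 6 and A = 1:
- Baseline: S50 = 50 + 6·ln 19 = 67.7, and MEP at 1.2 × 50 = 60 is 0.218 mV.
- RMT falls to 45 by a parallel shift (S50 = 62.7). At 1.2 × 45 = 54 the MEP is 0.191 mV, or −12%. At the old absolute intensity of 60 it is 0.391 mV, or +79%.
- RMT falls to 45 by proportional scaling (S50 = 60.9, k = 5.4). At 54 the MEP is 0.218 mV, or 0%. At 60 it is 0.458 mV, or +110%.

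Over all nine combinations of k and A, the session-specific measure changes by 0% (proportional) or −9% to −18% (parallel). At the fixed absolute intensity the change is +44% to +162%. M-max normalization does not alter this: it rescales the response, not the stimulus.

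**4. No true change, RMT set slightly wrong (same curves).** One point too high moves the 120% RMT amplitude by +11% to +25%; one point too low moves it by −10% to −21%. For two points the figures are +23% to +52% and −20% to −39%.

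**5. SMEP.** At any mA level reached at both visits, an unchanged curve gives a false change of 0%. If the peak or full-range area were analysed instead, and if the tolerated maximum rose by an assumed 5 to 10 mA (assumed midpoint 60 mA, slope 8 or 12), the peak would rise by 6% to 125% and the area by 38% to 162% with no change in excitability. The documents give neither a rise in tolerance nor a summary measure, so these figures are conditional.

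**6. Blinding claim.** Section 2.2 limits assessor blinding to the clinical assessments. The Discussion does not carry that limit over.

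**The case against.** The case for the plan is substantial.
- The lack of blinding is disclosed, and the defence is comparative: less susceptible, not immune.
- The plan has real safeguards in the stored hotspot, a numeric threshold rule, ten further MEPs at 120% RMT and M-max normalization.
- RMT must be determined at every session, so a threshold shift is recorded even though it is absent from the 120% amplitude. The five-level ladder can still show a change in slope relative to threshold.
- An article may leave outcome lists and scoring detail to a fuller document.
- These outcomes are exploratory in a 24-person pilot.

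Most of this stands and limits the point. It does not make the stated reason sufficient, because section 2.4.6 itself leaves the later-visit RMT and the SMEP stopping current open to influence.

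A reader might infer more than the documents support:
- *That the SMEP scale is also reset at each visit.* It is not. The steps are absolute mA, and only the upper end can move.
- *That twelve sessions of active stimulation will raise tolerance and mimic a spinal effect.* No tolerance data are given. Active TSS is below motor threshold and FES is applied at the ankle. This is a possibility only.
- *That the upper intensities will be unreachable in the most impaired participants.* The 140% step does need RMT at or below 100/1.4 = 71.4% of stimulator output. The documents give no distribution of RMT and do not link it to impairment.

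**Conclusion.** The point holds in a limited form. Both follow-up neurophysiological tests are run by someone who knows the arm, and standardized instruments reduce but do not remove influence on the later-visit RMT and the SMEP stopping intensity. Separately, the MEP at 120% of session-specific RMT cannot register a treatment effect confined to threshold as a gain. RMT, which would show it, is not named as an outcome. The SMEP ladder is sound if compared at common currents.

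The percentages rest entirely on assumed curves. They show direction and possible scale and are not estimates for this trial. The documents do not support a claim that these outcomes will hide or create an excitability change, only that they are open to it. The consequence is confined to the neurophysiological hypothesis and to planning based on it. The change is worth making but is not a condition for starting.

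**What to change.** 1. Score all EMG offline from files coded to hide arm and visit, with an automated peak-to-peak window set in advance. State that this protects scoring but cannot undo bias at acquisition. Cost: file coding.
2. Name RMT (% of stimulator output) as a corticospinal outcome and report it beside the 120% RMT amplitude. Cost: wording only, since it is already measured.
3. Compare SMEPs over the mA range reached at all of a participant's visits, not at the tolerated maximum. Cost: data above that range are set aside.
4. In the Discussion, limit the assessor-blinding statement to the clinical outcomes. In section 2.2, say that standardized equipment reduces operator influence but does not remove it. Cost: two sentences.

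None of these needs extra visits, pulses or assessors. Testing by someone who does not deliver the intervention and is kept unaware of the arm would also address acquisition bias, but it needs another trained operator.

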#### 2.3.1. Group 1: VFBT with Sham FES + Sham TSS.

Participants in this group will receive the sham simulation during VFBT. One electrode (5 × 10 cm) will be positioned over the thoracolumbar spine between T10-L2, and two inter-connected reference electrodes (5 × 5 cm) will be placed over the abdomen, medial to the anterior superior iliac spine. For FES, surface electrodes will be placed over the dorsi-flexors (5 × 5 cm) and the plantar-flexors (5 × 10 cm) on both sides. During the first 30 seconds of each session, there will be brief sensory-level stimulation, which will be dropped to 0 mA.

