#### 2.3.2. Group 2: VFBT with Active FES + Sham TSS.

Participants in this group will receive active FES for ankle muscles and sham TSS during VFBT. At the start of each session, motor threshold and maximum tolerable stimulation intensities will be determined for each muscle. FES will be delivered at a frequency of 30 Hz with a pulse width of 0.3 ms (MyndSearch, MyndTec Inc., Mississauga, ON, Canada). The closed-loop FES activates ankle muscles in response to real-time feedback from the Wii-Balance Board, which monitors the user’s COP. The filtered COP represents the body’s center of mass (COM). The body’s COM is continually monitored and the level of stimulation adjusted accordingly on a moment-to-moment basis, mimicking intact postural control. Stimulation intensity will vary between the motor threshold and 90% of the maximal tolerable intensity to facilitate the intended movements during balance tasks [37,38,47]. Sham TSS will be administered via a brief sensory-level ramp, then decreased to 0 mA, similar to group 1.

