#### 2.3.3. Group 3: VFBT with Active FES +Active TSS.

Participants in this group will receive the same active FES protocol described above, plus active TSS which will be applied using surface electrodes positioned over the T10–L2, with anterior electrodes placed over the abdomen medial to the anterior superior iliac spine (Fig 2). Stimulation will be delivered continuously at a sub-motor threshold at 30 Hz using biphasic, 1 ms pulse width (Stim2Go, Pajunk® GmbH, Germany) during VFBT.

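### Section 2.2 says participants stay blinded, but sham FES as described cannot be expected to mask participants to FES in the two contrasts with the sham arm

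*Protocol article*

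**What the plan says.** Section 2.2 (Randomization, allocation, and blinding) makes a general claim for all three arms: "Participants will remain blinded through the use of sham stimulation".

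Sections 2.3.1 to 2.3.3 then describe what each arm receives:

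- **Group 1 (sham FES, sham TSS).** Electrodes are placed as in the active arms. "During the first 30 seconds of each session, there will be brief sensory-level stimulation, which will be dropped to 0 mA".
- **Group 2 (active FES, sham TSS).** "At the start of each session, motor threshold and maximum tolerable stimulation intensities will be determined for each muscle". During training, "Stimulation intensity will vary between the motor threshold and 90% of the maximal tolerable intensity to facilitate the intended movements during balance tasks". For the spinal component, "Sham TSS will be administered via a brief sensory-level ramp, then decreased to 0 mA, similar to group 1".
- **Group 3 (active FES, active TSS).** "Participants in this group will receive the same active FES protocol described above". For the spinal component, "Stimulation will be delivered continuously at a sub-motor threshold at 30 Hz".

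Section 2.2 also says that clinical outcome assessors are blinded and that neurophysiological assessors are not. Section 2.4.4, headed as exploratory, lists the self-reported outcomes: MSWS-12, Falls Efficacy Scale-International (FES-I), ABC and a global rating of change.

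**The concern.** A sham keeps participants masked only if they cannot readily tell it from the active treatment. Here the active treatment is meant to contract the ankle muscles and assist movement, while the sham delivers no current after the opening seconds. The first can be felt and probably seen; the second cannot.

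If participants can tell which they have, those with active FES may expect more benefit and those with sham less. Scales that participants score themselves are directly open to this, and BBS, TUG and T25FW are partly open to it through effort. The Introduction hypothesises that TSS + FES will do better than FES alone and than sham. Section 2.6 and the Discussion say the effect sizes will feed the design and sample size of a fully powered trial. An effect size inflated by expectation would carry into that calculation, and a reader relying on section 2.2 would have no warning of it.

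**Working it through.** The plan gives no figure for blinding, so there is nothing to reproduce. The check sets the arm descriptions side by side and adds simple arithmetic on stimulation time.

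**Inputs.** Sham current: at most 30 s per session (2.3.1). Active training: 60 min in a session of about 90 min, 12 sessions (Table 2, item 9). Arms: 8 participants each, 24 in total (2.1).

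**1. Time with current on under sham.**
- Share of active training: 30 s / 3,600 s = 0.8%.
- Share of the whole session: 30 s / 5,400 s = 0.6%.
- Over the course: 12 × 30 s = 6 min, against 12 × 60 min = 720 min of active training.

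These are upper bounds. The 30 seconds fall at the start of the session, which may be before the training block.

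**2. What each arm can feel.**

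| | FES during training | TSS during training |
|---|---|---|
| Group 1 (n = 8) | 0 mA after at most 30 s, sensory level only | 0 mA after at most 30 s, sensory level only |
| Group 2 (n = 8) | at or above motor threshold | 0 mA after a brief sensory ramp |
| Group 3 (n = 8) | at or above motor threshold | continuous, sub-motor threshold |

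**3. Contrasts.**
- FES versus sham: differs in contraction-level FES. Masking is not expected.
- TSS + FES versus sham: the same FES difference, plus TSS. Masking is not expected.
- TSS + FES versus FES: differs only in sub-motor TSS against sham TSS. Masking is plausible, but sub-motor does not mean imperceptible and the document does not say that it is.

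Two of three contrasts are affected. Between them they involve all three arms.

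**4. Could inexperienced participants fail to notice?** Randomization follows baseline assessment (2.2), and each assessment time point includes a neurophysiology visit (2.5). There, M-max is obtained in soleus and tibialis anterior with maximal pulses to their nerves, and spinal stimulation is raised to the tolerance limit (2.4.6). Group 1 participants will therefore have felt evoked contraction in ankle muscles before their first training session.

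**5. Masking to TSS in Group 1.** No arm pairs sham FES with active TSS. A Group 1 participant who knows the three arms and notices that FES is absent can infer that TSS is sham too. Masking to TSS can hold, at best, only between Groups 2 and 3.

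**The case against.** The strongest points on the other side are these.

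- **Loss of masking is inferred, not stated.** What a participant makes of 0 mA depends partly on what they were told, and the consent material is not available. This stands as a limit on certainty. It does not rescue an unqualified claim, given the size of the difference in sensation and the baseline exposure.
- **A condensed article may omit things.** A reader might infer that Group 1 has no threshold and tolerance search, or that no masking check exists. The document does not establish either. Section 2.3.1 describes no search, but Table 2, item 12 describes individualised FES without limiting it to the active arms. The point does not need these inferences: it rests on what 2.3.1 to 2.3.3 state about current during training.
- **Efficacy is exploratory.** This is right. The main purpose is feasibility, acceptability, safety and adherence, so no confirmatory test is at risk.
- **Clinical assessors are blinded, and the Discussion's list of strengths names assessor blinding, not participant blinding.** Also right, and nothing here shows a defect in assessor blinding. It does not, however, protect scores that participants give themselves, and it protects effort-dependent tests only in part.

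A reader might also go the other way and call TSS + FES versus FES the masked comparison. The document does not support that either, as the perceptibility of the active TSS is not addressed.

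**Conclusion.** The point holds for FES. The participant-blinding statement in section 2.2 is broader than the sham described in section 2.3.1 can deliver. Participant masking cannot be expected in FES versus sham or in TSS + FES versus sham, two of the three contrasts. The consequence is possible expectation bias, chiefly in MSWS-12, FES-I, ABC and the global rating of change, and less certainly in BBS, TUG and T25FW. Neither its size nor its effect on a future sample size can be derived from the document.

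The conclusion assumes that contraction-level stimulation can be told from no current, which is a strong inference supported by the baseline testing. It does not extend to a claim that the whole trial is unblinded, that clinical assessors are unblinded, or that the feasibility and safety objectives are compromised.

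**What to change.** 1. **Reconcile section 2.2 with sections 2.3.1 to 2.3.3.** State that participant masking to FES is not expected to hold, and that masking to TSS is plausible only between the two active-FES arms and has not been verified.
2. **Qualify the reporting.** Present contrasts with the sham arm on the four self-reported outcomes as open to expectation bias, give a more tentative caveat for the effort-dependent tests, and repeat both wherever these effect sizes are used to plan the definitive trial.
3. **Measure sham credibility.** Add a brief item asking participants which arm they think they are in and how confident they are, for example after the first session and again with the TAM-2 form, and tabulate it by arm. In a pilot this is itself useful feasibility information.

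No stimulation setting needs to change for any of this.

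**Cost.** Some wording, a very short questionnaire item and possibly a small ethics amendment. The stated blinding becomes less favourable. Late guesses partly reflect perceived benefit, which is the reason for an early one. An early question may itself prompt suspicion during the remaining sessions, so its timing is a judgement for the team.
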